# Fasting in diabetes treatment (FIT) trial: study protocol for a randomised, controlled, assessor-blinded intervention trial on the effects of intermittent use of a fasting-mimicking diet in patients with type 2 diabetes

**DOI:** 10.1186/s12902-020-00576-7

**Published:** 2020-06-24

**Keywords:** Diabetes mellitus, type 2, Glycated hemoglobin a, Diet therapy, Fasting, Fasting-mimicking diet, Cost-effectiveness

## Abstract

**Background:**

Caloric restriction is an effective way to treat Type 2 diabetes (T2D). However, chronic and severe restriction of food intake is difficult to sustain and is known to promote slower metabolism. Intermittent and frequent fasting can exert similar metabolic effects, but may be even more challenging for most patients. A fasting-mimicking diet (FMD) is low in calories, sugars and proteins, but includes relatively high levels of plant based complex carbohydrates and healthy fats. The metabolic effects of such a diet mimic the benefits of water-only fasting. The effects of a FMD applied periodically in T2D patients are still unknown. The Fasting In diabetes Treatment (FIT) trial was designed to determine the effect of intermittent use (5 consecutive days a month during a year) of a FMD in T2D patients on metabolic parameters and T2D medication use compared to usual care.

**Methods:**

One hundred T2D patients from general practices in the Netherlands with a BMI ≥ 27 kg/m^2^, treated with lifestyle advice only or lifestyle advice plus metformin, will be randomised to receive the FMD plus usual care or usual care only. Primary outcomes are HbA1c and T2D medication dosage. Secondary outcomes are anthropometrics, blood pressure, plasma lipid profiles, quality of life, treatment satisfaction, metabolomics, microbiome composition, MRI data including cardiac function, fat distribution and ectopic fat storage, cost-effectiveness, and feasibility in clinical practice.

**Discussion:**

This study will establish whether monthly 5-day cycles of a FMD during a year improve metabolic parameters and/or reduce the need for medication in T2D. Furthermore, additional health benefits and the feasibility in clinical practice will be measured and a cost-effectiveness evaluation will be performed.

**Trial registration:**

The trial was registered on ClinicalTrials.gov. Identifier: NCT03811587. Registered 21th of January, 2019; retrospectively registered.

## Background

Type 2 diabetes (T2D) is a multifactorial disease, emanating from gene-environment interactions [1]. Diet quality and quantity are at the heart of its pathogenesis [2]. A positive energy balance, often caused by an excess of carbohydrates, leads to insulin resistance, impaired insulin secretion and hyperglycaemia [3–5]. Currently available medication for T2D influences glucose metabolism, but does not address the cause of T2D. In contrast, lifestyle interventions including dietary strategies can redress the underlying pathogenic mechanisms.

Caloric restriction and weight loss influence the course of T2D in a positive way. A loss of 5% of bodyweight or more reduces glycated haemoglobin (HbA1c), lipoprotein levels, and blood pressure [6]. Moreover, several studies have shown that T2D is not necessarily a chronic progressive disease and that remission can be achieved by continuous caloric restriction [7–9]. However, restriction of calories for a longer period of time can be difficult to sustain [10]. Prolonged caloric restriction has also been shown to reduce basal metabolic rate, even when adjusted for body weight reduction, indicating that continuous caloric restriction not only causes weight and lean body mass loss, but can also cause metabolic changes that may make it very difficult to reach and maintain a healthy weight and fat mass [11].

Preclinical experiments have shown various health benefits of intermittent and periodic fasting. For example, alternate day fasting (ADF) in mice reduces serum glucose and insulin levels and improves glucose tolerance [12, 13]. Human studies reveal similar effects, indicating that intermittent and frequent fasting can reduce calorie intake and fat mass [14], and decrease fasting glucose in patients with T2D [15, 16]. The health benefits of fasting are caused by several molecular mechanisms, including the reduction of ectopic fat storage, insulin levels, endogenous glucose production and IGF-1 [17]. Furthermore, it increases adipose lipolysis and fat oxidation, and glycerol and ketone bodies instead of glucose are used as preferred carbon sources. However, intermittent water-only fasting may be very difficult for patients to adhere to for long periods of time. Moreover, prolonged and frequent fasting may exacerbate pre-existing nutritional deficiencies, which may be unsafe for frail individuals [17], in addition to being associated with other potential risks in those extending the fasting period by skipping breakfast daily [18, 19].

Fasting-mimicking diets (FMDs) have been developed to mimic the endocrine and metabolic effects of complete fasting, while providing a modest number of calories [17]. To this end, FMDs comprise virtually no refined sugar or starch, low protein levels, complex carbohydrates and healthy fats, all from plant based sources [20–22]. In a pilot study, 38 healthy adults were randomised between three monthly, five-day cycles of FMD, or continuation of their normal diet; the FMD caused weight loss and reduced visceral fat [20]. In a larger study of 1 hundred healthy participants, three monthly, five-day FMD cycles reduced body weight, trunk and total body fat, lowered blood pressure and decreased IGF-1 [21]. A post hoc analysis showed a significant reduction in body mass index (BMI), blood pressure, triglycerides, and total and low-density lipoprotein cholesterol. In addition, in participants with an increased fasting glucose level (defined as 5.5 mmol/L or higher), the three FMD cycles brought glucose within the healthy range. The FMD was well tolerated without significant side effects [20, 21].

The above mentioned results suggest that a FMD could potentially be beneficial for patients with T2D, while minimizing the burden of frequent water-only fasting as well as side effects, such as slowing metabolism and loss of lean body mass. The FMD used in the Fasting In diabetes Treatment (FIT) trial is a five-day program providing patients with all the meals and containing ~ 1100 kcal on the first day and ~ 750 kcal on the following days [20, 21]. We will examine whether monthly five-day cycles of a FMD during a year improve metabolic parameters and/or reduce the need for medication in people with T2D treated by their General Practitioner (GP). We will also evaluate anthropometrics, blood pressure, plasma lipid profiles, quality of life, treatment satisfaction, metabolomics, microbiome composition and MRI data including cardiac function, fat distribution and ectopic fat storage. Furthermore, a cost-effectiveness evaluation will be performed and the feasibility in clinical practice will be measured. In the FIT trial, 1 hundred T2D patients from general practices in the Netherlands with a BMI ≥ 27 kg/m^2^, treated with lifestyle advice only or lifestyle advice plus metformin, will be randomised to receive the FMD plus usual care or usual care only. To our knowledge, we are the first to examine the impact of a FMD on a variety of health parameters in people with type 2 diabetes mellitus, who are treated by their GP.

### Primary study objective

To evaluate the effect of the intermittent use (5 consecutive days a month during a year) of a FMD on the combined primary outcomes HbA1c and antidiabetic medication dosage in T2D patients compared to usual care.

### Secondary study objectives

To evaluate the effect of the intermittent use (5 consecutive days a month during a year) of a FMD on anthropometrics, blood pressure, plasma lipid profiles, metabolomics, microbiome, MRI data (e.g. cardiac function and fat distribution), change in dietary pattern and physical activity in T2D patients compared to usual care.To perform a cost-effectiveness evaluation comparing the FMD with usual care.To evaluate the effects on quality of life and treatment satisfaction between the FMD group and the usual care group.To evaluate the feasibility in practice, measured as the percentage of compliant patients in the FMD group.

## Methods and design

### Study design

The study is designed as a randomised, controlled, assessor-blinded intervention trial on the effects of the intermittent use of a fasting-mimicking diet in T2D patients regularly treated in primary care. The trial is conducted in the Leiden University Medical Center (LUMC) in the Netherlands, according to the principles of the Declaration of Helsinki in accordance with the Medical Research Involving Human Subjects Act (WMO) and to the standards of Good Clinical Practice (GCP). The study was approved by the Medical Research Ethics Committee of the LUMC.

### Recruitment

Participants will be recruited from general practices in the area around Leiden and The Hague. General practice centres will be invited to collaborate in the study by contacting them through several care groups in the region of the province of South Holland. Potential participants will be identified by a computerised search of the general practices’ records. Lists of possibly eligible patients generated by the search will be reviewed by the GP and/or a physician assistant. Individuals likely to be ineligible, or unsuitable to approach because of co-morbidity or other practical or medical obstacles to participation, will be removed from this list. Potentially eligible participants will receive a patient information letter from their GP sent by regular mail with an invitation to participate in the study. Permission to disclose identifying data is given by sending back a response-leaflet to the investigator and/or the GP, using reply-paid envelopes. The GP and/or the physician assistant have the liberty to remind non-responders once.

Following agreement and disclosure of identifying data, potential participants will receive additional information from the investigators. When still interested in participation, an appointment for the first visit will be made, where the study will be fully explained and discussed. After written informed consent has been obtained, the participant will be screened further for eligibility.

Patients with T2D who hear from the study through other routes than the ones stated above and wish to participate, can participate if they fulfil the inclusion criteria and their GP does not have any objections. The inclusion period will last approximately 1,5–2 years, counting from the first inclusion.

If it is not possible to recruit enough participants through the various care groups, we can pre-select potential candidates in the anonymous routine healthcare database “ELAN data warehouse”. GPs in the Leiden/The Hague region share their anonymized patient data in this database. The ELAN data warehouse will then be used to preselect potential study participants from GPs who collaborate with us in this study. These GPs will identify and invite potential participants by matching electronic medical record code numbers.

### Study population

One hundred individuals (men or women) with T2D and a BMI ≥ 27 kg/m^2^, who are treated with lifestyle advice only and have a HbA1c > 48 mmol/mol, or who are treated with the combination of lifestyle advice and metformin, will be recruited for the study.

### Inclusion criteria

In order to be eligible to participate in the study, a participant must meet the following criteria:
Diagnosis of type 2 diabetesAge > 18 years and < 75 yearsBMI ≥ 27 kg/m^2^Treatment with lifestyle advice and meeting at least one of the following two criteria:
HbA1c > 48 mmol/molTreatment with metformin

### Exclusion criteria

A potential participant who meets any of the following criteria will be excluded from participation in this study:
Recent myocardial infarction (< 6 months)Creatinine clearance < 30 ml/min/1,73m^2^PregnancyContraindications for Magnetic Resonance Imaging (MRI)Allergy for nuts, sesame, soy or another ingredient of the dietHistory of syncope with calorie restriction in the pastAny significant other disease (at the discretion of the investigator)

### Screening

At screening for eligibility, medical history will be taken and a physical exam will be performed to collect information on in- and exclusion criteria. Fasting blood levels will be recorded for HbA1c, glucose, creatinine, aspartate aminotransferase (ASAT), alanine aminotransferase (ALAT), haemoglobin, red cell indices, leucocytes, thrombocytes. If it is unclear whether someone is eligible for inclusion, patient information can be requested from the GP, other specialists or the pharmacy.

### Intervention

Participants will be randomised to receive the FMD for 5 consecutive days a month during a year plus usual care or usual care only. The use of metformin will be continued during the study, including the FMD periods.

### The fasting-mimicking diet

The FMD is a meal replacement plan that mimics water-only fasting. It consists of ingredients that are generally regarded safe and is completely plant based. It consists of bars, soups and beverages aiming to achieve a consistent and effective short-term calorie restriction, while providing adequate micronutrients. An example of the meal plan can be found in Table 1. Very low protein and sugar content is essential for this diet. Complex carbohydrates and polyunsaturated fatty acids are its main components. It entails a 5 day regimen. For patients who weigh less than 100 kg, day 1 has ~ 1100 kcal (10% protein, 56% fat and 34% complex carbohydrate); days 2–5 are identical and provide ~ 750 kcal (9% protein, 44% fat, 47% complex carbohydrate). For patients who weigh more than 100 kg, the diet will be amplified with one bar a day (90 kcal) with similar characteristics as the rest of the diet. The diet is lactose and gluten free, but contains nuts, soy and tomato as ingredients. Water and herbal tea can be consumed without a limit during the 5 days of the diet. Coffee or tea containing caffeine are limited to one cup a day. All items to be consumed per day are placed in an individual package, which will prevent the participant from consuming components of one of the following days by accident.

**Table 1 Tab1:** Example meal plan of the fasting-mimicking diet for study participants

	Day 1	Day 2	Day 3	Day 4	Day 5
**Breakfast**	Tea	Tea	Tea	Tea	Tea
	Nut bar	Nut bar	Nut bar	Nut bar	Nut bar
	Algal Oil capsule				Algal Oil capsule
**Lunch**		Tea	Tea	Tea	Tea
	Tomato Soup	Mushroom Soup	Tomato Soup	Vegetable Soup	Tomato Soup
	Olives	Olives	Kale Crackers	Olives	Kale Crackers
	Kale crackers				
	Vitamin capsule	Vitamin capsule	Vitamin capsule	Vitamin capsule	Vitamin capsule
**Afternoon**	Tea	Tea	Tea	Tea	Tea
	Nut bar	Olives		Olives	
**Dinner**		Tea	Tea	Tea	Tea
	Minestrone Soup	Quinoa Mix Soup	Minestrone Soup	Quinoa Mix Soup	Minestrone Soup
	Choco crisp bar	Choco crisp bar		Choco crisp bar	
	Vitamin capsule	Vitamin capsule	Vitamin capsule	Vitamin capsule	Vitamin capsule
		Syrup for water flavouring	Syrup for water flavouring	Syrup for water flavouring	Syrup for water flavouring

### Usual care

To evaluate the feasibility of the use of the FMD in clinical practice, patients will be controlled by their general practitioner as usual and treated according to the Dutch treatment guideline for T2D for GP’s [23]. Medication dosage can be adapted by the GP as required to attain an HbA1c of 53 mmol/mol. If at any moment during the trial HbA1c is lower or higher than this target value, metformin (or any other prescription drug to reduce plasma glucose concentration) will be stopped, continued or increased at the discretion of the GP.

### Randomisation and treatment allocation

Randomisation will be performed after written informed consent and screening, when a participant is eligible based on the eligibility criteria. Participants will be randomised to receive the FMD in addition to usual care or usual care only. To ensure equal allocation of subgroups, stratification will be performed for gender and for weight < 100 kg and > 100 kg at baseline. Randomisation will be performed using permuted block randomization with blocks sizes 2 and 4.

Treatment allocation is computer generated via the electronic trial database in Castor EDC [24]. Allocation sequence is concealed by Castor EDC until randomisation of a participant. Castor EDC is used to assign participants to the different groups.

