### Primary outcome

The primary endpoints of the study are HbA1c and antidiabetic medication dosage. These primary endpoints will be combined to compare the total successful outcomes between the FMD group and the control group after 12 months of follow up. A successful outcome will be defined as any reduction in the antidiabetic medication dosage and/or a decrease of HbA1c of 5 mmol/mol or more. HbA1c and antidiabetic medication dosage will also be recorded after 6 months.

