### Power calculation

The number of participants that will be included in the study is limited to 100 (50 in each group). We computed expected effect sizes with a sample size of 100. As all participants will be asked to come in for T8, we work with a limited loss to follow-up of 10% [8], thus basing the calculations on 90 participants (45 in each group).

We computed the effect size that can be detected with 80% power for the binary endpoint, which is equal to one if either a lower dose of antidiabetic medication is used at the end of the study compared to the start, if HbA1c is at least 5 mmol/mol lower at the end compared to study start, or both.

The expected percentage of participants in the control group who will reach this endpoint is between 4 and 6% [8, 31]. For this power calculation, we assumed a percentage of 5% of participants in the control group who will reach the combined endpoint. With a significance level of 5 and 80% power, using a two-sided binomial test with 45 participants in each group, an absolute difference in percentages of 21% (i.e. 5% in the control group and 26% in the treatment group) can be detected.

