### Baseline data

Baseline data from the two groups will be compared on the following baseline values: age, gender, BMI and metabolic parameters. The values will be summarized using mean and standard deviation, or in case of an asymmetric distribution, by using median and interquartile range.

Hypothesis tests will be carried out using t-tests for independent samples, or, if the assumption of normality is violated, with a Mann-Whitney test. Multiple testing will be corrected for by using the Benjamini-Hochberg procedure. If the groups are found to be imbalanced on one or more covariates, then the following analyses will be adjusted for those covariates. Furthermore, the following analyses will be adjusted for gender and for weight < 100 kg or > 100 kg, since randomization is stratified for these values.

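### Entry route (lifestyle only or metformin) governs how the composite can be met and predicts 12-month dosage, yet it is neither a stratum nor a named covariate; the cost is precision, mainly for dosage

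*Protocol article*

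**What the plan says.** All references are to the protocol article.

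- **Inclusion criteria and Study population.** Entry requires "Treatment with lifestyle advice and meeting at least one of the following two criteria": HbA1c above 48 mmol/mol, or metformin. Metformin users have no HbA1c minimum.
- **Primary outcome.** Success is "any reduction in the antidiabetic medication dosage and/or a decrease of HbA1c of 5 mmol/mol or more". The Power calculation section measures the dose part against study start.
- **Randomisation and treatment allocation.** The strata are fixed: "stratification will be performed for gender and for weight < 100 kg and > 100 kg at baseline".
- **Baseline data.** "Baseline data from the two groups will be compared on the following baseline values: age, gender, BMI and metabolic parameters". Tests are corrected by Benjamini-Hochberg, and later analyses are adjusted for covariates found imbalanced. Adjustment for gender and the weight stratum is unconditional. Glucose-lowering treatment is not listed.
- **Primary and secondary outcomes.** HbA1c and dosage are compared by t-test or Mann-Whitney test on the 12-month values. Repeatedly measured outcomes also get mixed models.
- **Usual care and Medication use.** The GP may change dosage or start drugs at any time.

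**The concern.** The inclusion criteria create two groups with different access to the primary endpoint. A lifestyle-only participant starts at zero dose and can succeed only through HbA1c. A metformin user can succeed through either part, although the HbA1c part may be harder for someone who enters with a low value. Route is therefore linked to the composite by definition. It is also likely to be the strongest baseline predictor of 12-month dosage.

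The plan balances and adjusts for gender and weight but not for route. The only fallback depends on a significant baseline test of variables that do not include treatment. At stake are the precision of the dosage comparison, a possible chance shift in the realised estimates, and how clearly a pooled success rate can be read as dose reduction.

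**Working it through.** **1. The plan's own figure.** "With a significance level of 5 and 80% power, using a two-sided binomial test with 45 participants in each group", and "we assumed a percentage of 5% of participants in the control group who will reach the combined endpoint", the article finds that "an absolute difference in percentages of 21% (i.e. 5% in the control group and 26% in the treatment group) can be detected". With the pooled two-sided normal approximation, p̄ = (0.05 + 0.26)/2 = 0.155:

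z = [0.21 − 1.96·√(2·0.155·0.845/45)] / √[(0.05·0.95 + 0.26·0.74)/45] = 0.828, so power = 79.6%.

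The smallest treatment rate detectable with 80% power is 26.1%. The stated figure is reproduced.

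**2. How often the routes would be unbalanced.** The article does not give the metformin share; 40–80% is assumed. With 50 per arm and allocation independent of route (two independent binomials):

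| Metformin share | P(arms differ by ≥ 10 points) |
|---|---|
| 40% or 60% | 36% |
| 80% | 26% |

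**3. Would the baseline-test rule catch it?** Suppose treatment were among the tested variables, with an assumed 55% on metformin. The standard error of the difference is √(0.55·0.45·2/50) = 0.0995. A 10-point imbalance gives z = 1.005, p ≈ 0.31. Uncorrected p < 0.05 needs about 1.96 × 0.0995 = 19.5 points, and more after Benjamini-Hochberg. The likely imbalances would pass unnoticed.

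**4. Composite.** The shift in the success difference is the imbalance times the gap in success rate between routes. With no diet effect and 5% success overall, the gap is largest if every success is a metformin user: 5%/share.

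| Metformin share | Largest gap | Shift for a 10-point imbalance |
|---|---|---|
| 40% | 12.5 points | 1.25 points |
| 60% | 8.3 points | 0.83 points |
| 80% | 6.25 points | 0.63 points |

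Even an assumed 20-point imbalance with a 20-point gap gives 4 points, against the planned 21.

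Simulation (45 per arm, lifestyle-only share 10–50%, 100,000 runs per scenario):

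| | Unadjusted chi-square | Mantel-Haenszel stratified by route |
|---|---|---|
| Type I error | 4.8–5.0% | 3.8–4.2% |
| Power | about 84% | 82–84% |

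Among runs with at least 7 of 45 (about 16 points) imbalance in one direction, type I error of the unadjusted test reached at most about 6.5%.

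**5. Dosage at 12 months.** Assumed: share on metformin s = 0.4, 0.6 or 0.8; mean/SD among users 1000/500 or 1500/600 mg/day. If no lifestyle-only participant starts a drug, within-route variance is s·SD² and between-route variance is s(1−s)·mean². The detectable difference is 2.8·√(2·variance/45), using total variance when route is ignored and within-route variance when it is allowed for.

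Example (s = 0.6, 1500/600): within 216,000, between 540,000, so route explains 540/756 = 71%. The detectable difference is 513 mg/day ignoring route and 274 allowing for it.

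In the second scenario 20% of lifestyle-only participants start a drug, at an assumed mean of 1000 and SD of 300 mg/day. Their mean is then 200 and their variance 0.2·300² + 0.2·0.8·1000² = 178,000.

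| s, mean/SD | Nobody starts: ignoring → allowing (route share of variance) | 20% start: ignoring → allowing (route share) |
|---|---|---|
| 0.4, 1000/500 | 344 → 187 (71%) | 354 → 268 (43%) |
| 0.4, 1500/600 | 488 → 224 (79%) | 478 → 296 (62%) |
| 0.6, 1000/500 | 369 → 229 (62%) | 361 → 278 (41%) |
| 0.6, 1500/600 | 513 → 274 (71%) | 491 → 316 (59%) |
| 0.8, 1000/500 | 354 → 264 (44%) | 343 → 286 (30%) |
| 0.8, 1500/600 | 475 → 317 (56%) | 455 → 336 (46%) |

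A 10-point imbalance shifts mean dosage by 0.10 × (1000 to 1500) = 100–150 mg/day if nobody starts, or 0.10 × (800 to 1300) = 80–130 mg/day if 20% do.

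**The case against.** **Bias or inflated alpha.** A reader might infer that unbalanced routes bias the primary comparison. They do not: averaged over randomisation, type I error stays near 5%, and route adjustment brings no power gain for the composite. With an expected control success rate of 4–6% by either part, the gap between routes under no effect cannot be large. Its sign is not even certain, because metformin users may find the HbA1c part harder to meet. This stands, and it limits the composite concern to a modest one.

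**Lifestyle-only participants and need for medication.** A reader might also infer that they cannot inform this question. That is wrong: dosage is compared between arms at 12 months, so an avoided drug start counts. What they cannot show is a reduction from baseline.

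**Existing safeguards.** The imbalance rule exists, and metabolic parameters may include HbA1c. It remains weak (step 3) and does not list treatment. The mixed models could absorb stable differences in dosage if the baseline value enters as a repeated outcome, which the article does not state. The 12-month two-group test has no such protection, and the composite is not modelled this way.

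**Left to a fuller document.** Detail on covariates often is. But this article itself fixes the strata, the unconditional covariates and the list of baseline comparisons, and route is in none of them.

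**Strata.** Few strata at 100 participants is a defensible choice, and weight has a reason, since the diet differs at 100 kg.

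**Conclusion.** The point holds as one of efficiency and interpretation, not of validity. Route determines which parts of the composite are open to a participant and predicts 12-month dosage, and the plan neither balances it nor names it as a covariate. For the composite the consequence is small: about 0.6–1.3 points under no effect for a 10-point imbalance, with the planned sample size and the 21-point difference essentially unaffected.

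For the 12-month dosage test it is material. The detectable difference falls from about 344–513 to 187–317 mg/day if nobody on lifestyle advice starts a drug, which is the best case, and from about 343–491 to 268–336 mg/day if 20% do. Metformin share, doses and start rate are assumptions, because the article gives none of them. The normal approximation is also rough for a dosage with many zeros, so the figures show the order of the gain rather than its exact size.

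**What to change.** In Baseline data and in Primary and secondary outcomes, before any unblinded analysis:

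- **Dosage.** Name baseline glucose-lowering treatment, preferably baseline dosage, as a fixed covariate in the 12-month analysis, alongside gender and weight stratum. Keep all participants in this comparison.
- **Composite.** Use a route-stratified or adjusted analysis suited to few events. Report the composite descriptively by entry route. Any statement about dose reduction should refer to participants on metformin at baseline.
- **Stratification.** Add route only if randomisation is still open. One year of follow-up ending in June 2021 implies that inclusion closed around June 2020, when the article appeared, so this is probably moot.

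Cost: no new data, since medication is recorded at screening and T0, and no change in sample size. The planned rates imply 45 × 0.05 + 45 × 0.26 = 2.25 + 11.7 ≈ 14 events. Treatment, gender, weight and route then leave about 14/4 = 3.5 events per parameter, which is why an ordinary logistic model is a poor choice. The stratified test is slightly conservative. If route is added as a stratum, 4 strata become 8, with a few more incomplete blocks.
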